## Abstract

**Background:**

The number of solid organ transplants in Canada has increased 33% over the past decade. Hospital readmissions are common within the first year after transplant and are linked to increased morbidity and mortality. Nearly half of these admissions to the hospital appear to be preventable. Mobile health (mHealth) technologies hold promise to reduce admission to the hospital and improve patient outcomes, as they allow real-time monitoring and timely clinical intervention.

**Objective:**

This study aims to determine whether an innovative mHealth intervention can reduce hospital readmission and unscheduled visits to the emergency department or transplant clinic. Our second objective is to assess the use of clinical and continuous ambulatory physiologic data to develop machine learning algorithms to predict the risk of infection, organ rejection, and early mortality in adult heart, kidney, and liver transplant recipients.

**Methods:**

Remote Mobile Outpatient Monitoring in Transplant (Reboot) 2.0 is a two-phased single-center study to be conducted at the University Health Network in Toronto, Canada. Phase one will consist of a 1-year concealed randomized controlled trial of 400 adult heart, kidney, and liver transplant recipients. Participants will be randomized to receive either personalized communication using an mHealth app in addition to standard of care phone communication (intervention group) or standard of care communication only (control group). In phase two, the prior collected data set will be used to develop machine learning algorithms to identify early markers of rejection, infection, and graft dysfunction posttransplantation. The primary outcome will be a composite of any unscheduled hospital admission, visits to the emergency department or transplant clinic, following discharge from the index admission. Secondary outcomes will include patient-reported outcomes using validated self-administered questionnaires, 1-year graft survival rate, 1-year patient survival rate, and the number of standard of care phone voice messages.

**Results:**

At the time of this paper’s completion, no results are available.

**Conclusions:**

Building from previous work, this project will aim to leverage an innovative mHealth app to improve outcomes and reduce hospital readmission in adult solid organ transplant recipients. Additionally, the development of machine learning algorithms to better predict adverse health outcomes will allow for personalized medicine to tailor clinician-patient interactions and mitigate the health care burden of a growing patient population.

**Trial Registration:**

ClinicalTrials.gov NCT04721288; https://www.clinicaltrials.gov/ct2/show/NCT04721288

**International Registered Report Identifier (IRRID):**

PRR1-10.2196/26816

## Introduction

Solid organ transplant (SOT) is the standard therapy for select patients with severe end organ dysfunction. During the transition from pre- to posttransplant, recipients are introduced to a number of new medications and medical issues. In light of this complexity, early hospital readmission is common, ranging from 18% to 47% [1-3]. In addition to an increased burden on the health care system, early hospital readmission is associated with increased patient morbidity and mortality [4]. Although some readmissions are unpredictable and unavoidable, as many as half of early readmissions may be preventable [4].

Mobile health (mHealth) technologies such as smartphones and wearable devices hold promise to reduce hospitalization and improve patient outcomes through real-time monitoring, prompting timely clinician intervention that cannot be replicated in traditional outpatient care [5]. A recent systematic review showed mHealth apps improve patient self-management and reduce rates of rehospitalization in adults with cardiovascular disease [6]. Previous work from our group has shown that mHealth technology is safe, feasible, and associated with a 50% relative risk reduction in rehospitalization in adults with heart failure [7]. We anticipate that SOT recipients would also benefit from improved monitoring and removal of communication barriers as the most common reasons for readmission (eg, infection, rejection, elevated blood pressure, and metabolic derangements such as renal, glucose, and electrolyte abnormalities) and mortality may be mitigated by clinical intervention [1,2,5,8]. Additionally, medication adherence is critical in transplant patients to prevent graft rejection [9,10]. Enhanced and clear communication is likely to lead to improved patient outcomes.

Over the past decade, the number of SOTs in Canada has increased by 33% [11]. As transplant program volumes continue to grow, the need to reduce hospital readmissions is critical both for patients and to avoid straining the health care system. Building upon prior research in which the safety and feasibility of mHealth technologies in adult patients with heart transplants was demonstrated [12], larger scale clinical data is needed to determine whether this technology reduces hospital readmissions.

In the transplant population, it is likely that remote monitoring will improve medication adherence/adjustments and will allow for identification of early decompensation and reduce preventable hospital readmissions. Thus, this study will determine if an innovative mHealth intervention designed to improve patient-clinician communication reduces unnecessary hospital readmission and visits to the emergency department (ED) and transplant clinic when used in addition to the standard of care telephone communication system. We will also incorporate clinical and continuous ambulatory physiologic data collected as part of the mHealth intervention to develop machine learning (ML) algorithms capable of identifying early indicators of adverse outcomes in adult patients with heart, kidney, and liver transplants.

Therefore, we hypothesize that the delivery of personalized communication using an mHealth app will improve patient self-management, resulting in a reasonable reduction in preventable hospital readmission and unscheduled visits to the ED and transplant clinic of 50%. With tailored communication through the mHealth app, we expect fewer standard of care phone messages for patients in the intervention group, and patients with higher activity levels (average daily step count) pretransplantation will have lower index hospitalization length of stay. Finally, the large data set collected from this study will allow novel ML-derived risk prediction models to more accurately predict adverse outcomes (eg, organ rejection, infection, and death) compared to conventional regression models.

## Methods

### Overview

Remote Mobile Outpatient Monitoring in Transplant (Reboot) 2.0 is a registered (ClinicalTrials.gov NCT04721288) two-phased single-center study. It has also been approved by the University Health Network (UHN) Research Ethics Board (REB 20-6082.0.1). The first phase will consist of a 1-year concealed randomized controlled trial of 400 adult SOT (heart, kidney, or liver) recipients. Currently, the Ajmera Transplant Centre at the UHN (a large academic teaching site in Toronto, Canada) uses paper medical administration records to alter immunosuppressive medications, and patients generally record their vitals by pen and paper, both of which may be error prone. Additionally, health care providers and patients with transplants rely on a telephone-based (“Easy Call”) method of communication, wherein patients leave a message for their health provider when issues arise. The integration of medication and vitals tracking, as well as patient-provider communication into a single mHealth app may decrease errors and improve patient outcomes. To test this, participants will be randomized to receive either personalized communication using an mHealth app in addition to the Easy Call system (intervention group) or Easy Call standard of care (control group; see Figure 1). In the second phase of Reboot 2.0, the data set from the 400 patients with SOTs collected as part of phase one will be evaluated in an attempt to identify early markers of rejection, infection, and graft dysfunction posttransplant.

**Figure 1 figure1:**
[figure not shown]
Proposed study flowchart. UHN: University Health Network.

### Participants

The UHN in Toronto, Canada conducted over 700 transplants in 2019, including approximately 225 liver transplants, 225 kidney transplants, and 40 heart transplants. Based on this distribution, we expect to recruit 150 to 200 liver transplant, 150 to 200 kidney transplant, and 40 to 50 heart transplant recipients from the SOT waiting list at the UHN. Inclusion criteria include heart, kidney, or liver transplant recipients; age ≥21 years; the ability to use a smartphone (Apple iOS); and English speaking. Exclusion criteria include patients with poor health literacy (defined as a reading level less than grade 5), transfer to a non-UHN hospital for follow-up and management, and an inability to follow instructions from the mHealth app.

### Screening and Recruitment

Patients on the UHN transplant waiting list will be screened by study personnel for participation in this study. Consent and enrollment will be completed while participants are still on the transplant waiting list. Prior to discharge from the index hospitalization, patients will be randomized to either the intervention or control group. All patients will be given an Apple Watch at the time of discharge from their index hospitalization to record continuous ambulatory physiologic data. The use of smartwatch technology will allow autonomous step count tracking and rapid clinician intervention in response to patient inactivity, heart rate monitoring, heart rate variability, intermittent electrocardiography, and the development of robust ambulatory physiologic data that can power predictive ML algorithms for adverse patient outcomes.

### Randomization

Concealment of allocation will be ensured by the use of a centralized 24-hour internet-based computerized randomization system. Participant will be the unit of randomization, and to protect against imbalance in known prognostic factors between groups, stratified randomization will be used. Stratification will be based on age (ie, 18-31 years, 31-50 years, or >50 years of age), organ transplanted (ie, heart, kidney, or liver), listing status (ie, urgent transplant or nonurgent transplant), and history of organ replacement therapy (ie, left ventricular assist device or dialysis). Block randomization, using four blocks, will ensure balance between participants randomized to the intervention and control groups.

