### Statistics

Currently at the UHN, approximately 20% of patients are readmitted to the hospital within 30 days post SOT. In general, these patients are readmitted following presentation to either the ambulatory transplant clinic or ED. Although we do not have data on the number of patients that present to the ambulatory transplant clinic within 30 days post SOT, previous work has shown ED visits at 30 days to vary greatly between SOT groups (eg, as low as 17% for patients with kidney transplants, and as high as 44% for patients with liver transplants) [24,25]. Given this variability, we hypothesized a conservative estimate of 20% for our 30-day composite end point. To observe a 50% relative risk reduction, from 20% to 10%, for the 30-day composite end point, at an alpha of .05 and power of 0.8, 199 participants will need to be recruited for each group.

We will evaluate all outcomes using the intention-to-treat analytical approach. A Cox proportional hazard model will be used to evaluate the effect of the mHealth app on posttransplant unplanned readmission and ED and unscheduled transplant clinic visit rates (primary outcome). Results of this analysis will be reported as hazard ratios with 95% CIs. Kaplan-Meier curves will be used to depict freedom from unplanned readmission. Subsequent to running the Cox proportional hazard model, a logistic regression model will be used to analyze unplanned readmission rates at the prespecified time points of 30 days, 3 months, and 1 year. Results of the logistic regression model will be reported using odds ratios and 95% CIs.

Generalized linear models to estimate the mean difference in the intervention compared to the control group will be used to estimate the impact of personalized communication through the mHealth app on posttransplant patient-reported outcomes (secondary outcomes).

To avoid spuriously inflated estimates of treatment effect, an interim analysis will be conducted when 50% of participants are enrolled and have completed follow-up. The results of this analysis will be reviewed by an independent data monitoring committee. The O’Brien-Fleming stopping rule will be used based on our primary outcome and requires a *P*≤.007 [26]. This conservative rule will avoid premature trial termination unless a large treatment effect is observed.

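### The stratified block randomization cannot be run consistently as written: age 31 sits in two bands, the youngest band starts below the eligibility age, and four blocks cannot serve at least 36 strata

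*Protocol article*

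**What the plan says.** **Randomization.** Allocation is by a centralized internet-based system, stratified on four factors:
- Age: "Stratification will be based on age (ie, 18-31 years, 31-50 years, or >50 years of age".
- Organ: "organ transplanted (ie, heart, kidney, or liver".
- Listing status: "listing status (ie, urgent transplant or nonurgent transplant".
- History of organ replacement therapy, naming left ventricular assist device (LVAD) and dialysis. The section does not say whether these are one category or two.

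On blocking it says: "Block randomization, using four blocks, will ensure balance between participants randomized to the intervention and control groups". It gives no block size.

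**Participants.** Eligibility covers "heart, kidney, or liver transplant recipients; age ≥21 years". The expected intake includes 40 to 50 heart recipients; Overview gives 400 patients in all.

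**Screening and Recruitment; Intervention.** Patients consent and enroll on the waiting list and are randomized before discharge from the index stay. Only the intervention arm can message the care team, which answers through a provider dashboard.

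**Statistics.** "A Cox proportional hazard model will be used to evaluate the effect of the mHealth app on posttransplant unplanned readmission". No stratification factor is named for the model, and none is ruled out.

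**The concern.** A stratified allocation rule has to send every eligible patient to exactly one list, and each list has to have blocks of its own. The text does neither. For a patient aged 31 the list is undefined. The youngest band admits ages that eligibility excludes, so either the band or the eligibility age is misstated. The blocking phrase gives a number of blocks where a block size would be expected, and that number is smaller than the number of strata.

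This is the operative allocation rule. Whoever configures the randomization system would have to guess the age boundary, the number of history levels and the block size, and those guesses could differ from what is later reported or used in an analysis by stratum. If the guess is fixed blocks of four, a further issue follows: some assignments become predictable to staff who see earlier ones.

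**Working it through.** **1. Age bands against eligibility.** The bands are 18–31, 31–50 and over 50; eligibility is 21 or older.
- Age 31 satisfies both of the first two bands, so they are not mutually exclusive.
- Ages 18, 19 and 20 lie in the first band but cannot be enrolled.

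**2. Number of strata.** Age has 3 levels, organ 3 and listing status 2. The levels of history are not stated, so both readings are shown.
- Yes/no: 3 × 3 × 2 × 2 = 36 strata; 400/36 = 11.1 patients each on average.
- LVAD/dialysis/none: 3 × 3 × 2 × 3 = 54 strata; 400/54 = 7.4 each.

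**3. Can four blocks serve them?**
- Four blocks in total: each stratum needs at least one block, and 4 is less than 36.
- Four blocks per stratum: 11.1/4 = 2.8 patients per block on average, which is not a usable block size for 1:1 allocation, and stratum sizes are not known in advance.
- Blocks of size four: workable, and probably what was meant, but not what is written.

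**4. Predictability if blocks are fixed at four (1:1).** A block has 6 equally likely orders. The fourth allocation is always determined. The third is determined when the first two match, which happens in 2 of 6 orders. Expected determined allocations per block are 1 + 1/3 = 4/3, and (4/3)/4 = 1/3 of allocations in complete blocks.

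**5. Overall balance if blocks are fixed at four.** Only the last, incomplete block of each stratum contributes to the arm difference. With 0, 1, 2 or 3 patients in it, the variance of the difference is 0, 1, 4/3 or 1. (With two patients the difference is ±2 with probability 1/3, otherwise 0.) If the four cases are equally likely, the mean is (0 + 1 + 4/3 + 1)/4 = 0.833.
- 36 strata: variance 36 × 0.833 = 30, SD 5.5. A simulation with 400 patients gave SD 5.4 and a 95th percentile of the absolute difference of 10, both for equal strata and for the skewed case mix in step 6.
- 54 strata: variance 54 × 0.833 = 45, SD 6.7.
- Simple randomization: SD √400 = 20.

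**6. Balance within heart cells.** With history yes/no, the heart cells number 3 × 2 × 2 = 12. Then 40/12 = 3.3 and 50/12 = 4.2 patients per cell, about one block each. A cell with three patients always splits 2:1; a cell with two puts both in the same arm one time in three. Under an assumed skewed mix (age 10/30/60%, urgent 20%, history 40%, heart 11%), 12 of the 36 cells expect fewer than 4 patients.

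**7. Sample size.** For 20% against 10%, two-sided alpha 0.05, power 0.80 and pooled variance: [1.96 × √(2 × 0.15 × 0.85) + 0.842 × √(0.20 × 0.80 + 0.10 × 0.90)]² / 0.10² = 199 per group. This reproduces the article's figure, and nothing above changes it.

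**The case against.** **These are wording slips.** An article may simplify, and block sizes are often kept out of print on purpose. That stands for the missing block size. It does not excuse text that is present and contradictory: the overlapping bands, the lower bound of 18 and the count of four blocks are stated, not omitted.

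**Predictability is remote.** It depends on reading the phrase as fixed blocks of four. Allocation is centralized, and a guesser would have to follow 36 or more interleaved lists, with about one block in each heart cell. Most of this stands: the one-third figure is a property of the scheme, not an estimate of bias. The residual exposure comes from having one center and a care team that sees who has messaging access.

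**Sparse strata defeat the promised balance.** A reader might infer this from 36 cells and 400 patients. The calculation does not support it: the article promises balance between the two groups, and blocks of four would deliver that well. Only balance within small cells is weak.

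**The primary Cox model ignores the strata.** A reader might infer this too, because the article cites 30-day ED visit rates "as low as 17% for patients with kidney transplants, and as high as 44% for patients with liver transplants" and names no covariates. But Statistics excludes none either, and a condensed article commonly leaves model covariates to the full protocol or analysis plan, which are not shown. The model cannot be called unadjusted on this evidence. Nor can a power loss be charged to the plan: any gain from stratifying rests on assumed heart and 1-year rates and is small near the planned 50% reduction. With one such set of assumptions (88 kidney, 88 liver and 23 heart patients per arm; 30-day rates 17/44/25% and 1-year rates 40/75/60% for kidney/liver/heart), power at a hazard ratio of 0.5 was 99.7% with and without organ stratification.

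**Conclusion.** The point holds for the allocation rule. Three defects rest on the text alone: two age bands share age 31, the youngest band starts below the eligibility age, and four blocks cannot serve the strata that the same section creates. The count of 36 assumes a yes/no history factor and 54 a three-level one; the conclusion is the same under both.

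The remaining consequences are conditional and modest. If fixed blocks of four are intended, one third of allocations in complete blocks are determined by earlier ones and the heart cells are thinly balanced, while the overall arm difference stays small. Neither the sample size nor the validity of the trial is in question. The rule should be corrected before the randomization system is configured. The handling of strata in the analysis is a recommendation only.

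**What to change.** - **Age bands.** Reconcile the bands with the eligibility age and make them mutually exclusive. If eligibility stays at 21, for example: 21–30, 31–50, over 50.
- **History factor.** State its levels: yes/no, or LVAD, dialysis, none.
- **Blocks.** Replace the reference to four blocks with permuted blocks of randomly varied small size within strata. Keep the sizes inside the concealed central system; the article need only say that they vary.
- **Analysis (recommended).** Stratify the Cox model by organ, and enter age band, listing status and organ-replacement history as covariates. Carry the randomization factors into the logistic models too.

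The cost is system configuration before the first patient is randomized, plus a few sentences of text. No new data are needed, since every factor is known at randomization. If enrollment has already started, report the rule actually programmed, including how patients aged 31 were assigned.

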### Intervention

Both groups will have access to the Reboot 2.0 mHealth app and receive generic notifications (eg, for achieving a daily step goal) as well as the option to log vital signs (eg, blood pressure, heart rate, weight, and temperature); however, only participants in the intervention group will receive tailored communication. This aspect of the intervention is designed to improve patient care by providing organ-specific educational material, a medication list, and weekly updates on fitness status (eg, heart rate and step count) with the overall goal of improving patient self-care and management. This will also be supported through the delivery of personalized notifications (eg, app use incentives, appointment reminders, medication changes, and clinical care updates) through the app. The use of reminder notifications and the smartphone calendar will help avoid missed tests and appointments in the intervention group. More importantly, the intervention group will have access to active communication with the transplant care team, including the ability to send asynchronous messages for nonurgent issues. Asynchronous messaging will be available as an integrated function within the mHealth app, accessible by the patient on their smartphone device and by the care team through the app’s provider dashboard. The care team will respond to messages within 48 hours (the same time frame as the standard of care system) and copy message conversations from the provider dashboard to the electronic medical record, avoiding the need for verbal message transcription. This will reduce the need for patients and clinicians to leave messages on the standard of care system and therefore improve patient-provider communication. We expect that improving patient education and self-management, and alleviating communication barriers will facilitate earlier recognition of decompensation and avoid preventable hospitalizations and ED visits.

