## Discussion

Reboot 2.0 will build on previous pilot work that demonstrated the safety and feasibility of an mHealth intervention in adult patients with heart transplants [12]. It will be the first study to examine the clinical impact of this mHealth app on a large group (n=400) of diverse (heart, kidney, and liver) SOT recipients. In particular, the clinical trial phase of this research project will determine if leveraging an innovative and patient-centric mHealth app and smartwatch technology reduces hospital readmission and improves patient-reported outcomes as well as patient and graft survival in this population. If so, the mHealth app may be mobilized on a larger scale to reduce the burden on the health care system of a growing patient population. The results of this phase may be limited by its single-center design; however, the Ajmera Transplant Centre at the UHN is the largest in North America and therefore will allow for a diverse and representative participant population.

Phase two of Reboot 2.0 is particularly novel in that it will result in the development of a data registry from 1 year of clinical data, patient-reported data collected through the mHealth app, and ambulatory physiologic monitoring using the Apple Watch from 400 patients with SOTs. This will allow us to develop predictive ML algorithms to better predict adverse health outcomes in these patients, and the subsequent application of these algorithms will allow for more personalized transplant medicine and tailored clinician-patient interactions.

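### Both arms receive the app and the smartwatch, so the trial can estimate the effect of tailored communication and messaging, not of the app and smartwatch that its analysis and Discussion name

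*Protocol article*

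**What the plan says.** The protocol article describes the arms in four places.

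- **Abstract, Methods.** The intervention arm has personalised communication through the app on top of phone communication. The comparator is "standard of care communication only (control group").
- **Methods, Overview.** Participants receive "personalized communication using an mHealth app in addition to the Easy Call system (intervention group) or Easy Call standard of care (control group"). The app is named only on the intervention side.
- **Methods, Screening and Recruitment.** Every participant is given an Apple Watch at discharge from the index admission. One stated use of the watch is "rapid clinician intervention in response to patient inactivity", with no mention of arm.
- **Methods, Intervention.** "Both groups will have access to the Reboot 2.0 mHealth app and receive generic notifications", with optional logging of vital signs. However, "only participants in the intervention group will receive tailored communication". Active communication with the care team, including asynchronous messages, belongs to the intervention group.

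The target of inference is also worded in more than one way. The Introduction's hypothesis concerns personalised communication delivered by the app. In Statistics, the primary Cox model is said to evaluate the app's effect, whereas the analysis of patient-reported outcomes is said to estimate the impact of personalised communication through the app. The Discussion says the trial phase "will determine if leveraging an innovative and patient-centric mHealth app and smartwatch technology reduces hospital readmission".

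**The concern.** A randomised comparison estimates the effect of what differs between the arms. Anything given to both arms is held constant, and its effect cannot be recovered from the contrast. Here the watch and the base app are held constant, while the primary analysis and the Discussion attribute the result to the app and, in the Discussion, to the smartwatch as well.

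What is at stake is what the result can be used for. The Discussion proposes wider deployment of the app if the trial succeeds. A positive result would support adding tailored communication and messaging for patients who already have the app and watch. It would not show what the app or watch does compared with telephone care alone. A null result would not show that the app and watch are without effect.

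Two smaller matters follow. The text leaves open whether clinicians act on watch data in the control arm; if they do, that is an active component shared by both arms. And the planning rate for controls is taken from current practice, in which, according to the Overview, vital signs are recorded on paper and messages go by telephone.

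**Working it through.** **Step 1: components by arm, as the text gives them**

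| Component | Intervention | Control | Source |
|---|---|---|---|
| Easy Call | Yes | Yes | Standard of Care |
| Apple Watch | Yes | Yes | Screening and Recruitment |
| Base app, generic notifications, vital-sign logging | Yes | Yes | Intervention |
| Organ-specific education, medication list, weekly fitness updates, personalised notifications | Yes | No | Intervention |
| Asynchronous messaging with the care team | Yes | No | Intervention |
| Clinician contact triggered by inactivity on the watch | Not stated by arm | Not stated by arm | Screening and Recruitment |

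The first three rows cancel in the comparison. The next two are what is randomised. The last cannot be placed from the text.

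**Step 2: compare with the stated targets**

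- Introduction (personalised communication through the app): matches the randomised rows.
- Statistics, patient-reported outcomes (personalised communication through the app): matches.
- Statistics, primary Cox model (the app): too broad, because the base app is in both arms.
- Discussion (app and smartwatch technology): too broad, because the base app and the watch are both in both arms.

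**Step 3: reproduce the planned sample size**

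Inputs from Statistics: 20% versus 10% at 30 days, alpha .05, power 0.8. The article does not state sidedness; two-sided is assumed. With pooled variance under the null, no continuity correction and p̄ = 0.15:

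n = [1.960·√(2·0.15·0.85) + 0.8416·√(0.20·0.80 + 0.10·0.90)]² / 0.10²
= [1.960·0.5050 + 0.8416·0.5000]² / 0.01
= 198.96, so 199 per group.

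This is the stated figure. There is no arithmetic error.

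**Step 4: illustrate sensitivity to the control rate**

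The 20% is current readmission practice at the centre. The article gives no rate for controls who have the app and watch, so the lower rates below are assumptions. The formula is

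power = Φ{ [ |p₁ − p₂|·√n − 1.960·√(2p̄(1 − p̄)) ] / √(p₁(1 − p₁) + p₂(1 − p₂)) }, with n = 200 per group.

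Example, 16% versus 10%: (0.06·√200 − 1.960·√(2·0.13·0.87)) / √(0.1344 + 0.0900) = (0.8485 − 0.9322)/0.4737 = −0.177, and Φ(−0.177) = 0.43.

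| Assumed control rate | Power, intervention arm at 10% | Power, 50% relative reduction kept |
|---|---|---|
| 20% | 80% | 80% |
| 18% | 64% | 75% |
| 16% | 43% | 69% |
| 15% | 33% | 66% |

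The rate could also lie above 20%. Statistics calls 20% conservative for a composite wider than readmission and cites 30-day emergency visits of 17% to 44%, depending on organ. Assume a 30% usual-care composite and 15% in the intervention arm. If the app and watch then lower the control rate by a tenth, 27% versus 15% gives 84% power; if by a fifth, 24% versus 15% gives 62%.

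**The case against.** The strongest reply is that the design is deliberate and already disclosed. Phase two needs ambulatory data from all 400 participants, so both arms must carry the watch and app. Holding a platform constant and randomising its communication functions is a legitimate design. The Intervention section says openly what is shared, and the Introduction already states the narrower hypothesis. The Abstract and Overview can be read as naming the communication channel of each arm, in which case they are incomplete summaries rather than contradictions. All of this stands. It limits the point to how the primary effect and the conclusion are worded and how controls are described; it does not rescue the statements in Statistics and the Discussion.

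On watch-triggered contact, the sentence sits in a recruitment paragraph and describes what the technology allows. Procedures by arm may be in the full protocol or in Figure 1, neither of which is shown. That is fair, so this part is only a request to reconcile two sections.

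Two stronger readings are tempting, and the documents support neither. A reader might infer that the trial is underpowered because controls have the app and watch. But the lower control rates are assumptions, the composite rate may exceed 20%, and 199 per group reproduces. A reader might also infer that the 50% reduction was borrowed from a comparison whose controls had no technology. The article does not describe the comparator in the heart failure work, and the Introduction also cites evidence that up to half of early readmissions may be preventable. No claim is made here about the origin of the 50%.

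**Conclusion.** Wrong as written, in a limited way. The primary-effect wording in Statistics and the concluding claim in the Discussion attribute to the randomised comparison effects that it cannot estimate: the watch entirely, and the app apart from its tailored communication and messaging functions. This follows from the article's own text and needs no assumption. The Abstract and Overview add to the problem by not mentioning the app and watch that controls receive.

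The trial remains valid for the effect of tailored communication and messaging added to base app, watch and Easy Call. Any effect on power is unknown in size and direction. The illustrative range for controls at 18% to 15% is 64% to 33% with the intervention arm fixed at 10%, or 75% to 66% with the relative reduction kept; it does not show that the stated 80% is wrong.

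**What to change.** 1. Describe controls in the same way throughout, including the Abstract and Overview: Easy Call plus base app plus watch.
2. In Statistics, restate the primary effect as that of tailored communication and messaging through the app, matching the Introduction's hypothesis and the wording already used for patient-reported outcomes.
3. In the Discussion, restate the conclusion in the same terms and drop the claim that the trial tests the smartwatch, or the app as such.
4. Reconcile Screening and Recruitment with Intervention on whether watch-triggered clinician contact occurs in one arm or both. Which it should be is for the investigators to decide.
5. Note beside the sample size that the 20% comes from current practice, not from controls with app and watch. If a power sensitivity is added, show rates on both sides of 20% and label it illustrative.

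These are changes of wording, plus an optional short table. Arms, sample size and data collection stay as they are. The cost is a narrower claim.
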